### Procedure

The healthcare professionals (oncologist or nurse) will inform eligible participants about the study (see Fig. 1). The research assistant will follow up to inform the patients about the details of the study and asks them for oral and written informed consent. Patients who agree to participate will be asked to fill in: (1) the socio-demographic and medical history form, (2) the World Health Organization Quality of Life - Assessment Bref (WHOQOL-BREF), (3) the European Quality of Life-5 Dimensions-5 Levels (EQ-5D-5 L), (4) the Hospital Anxiety-Depression Scale (HADS) Questionnaire, (5) the Breast Cancer Knowledge Test (BCKT). Participants who are illiterate will be giving an oral consent and a thumb print in lieu of a signature, in line with recommendations from WHO [23].

**Fig. 1 Fig1:**
[figure not shown]
Flowchart of The Procedure

Participants in the control group will receive treatment as usual (TAU), while the intervention group will receive the PERANTARA package (which consists of printed and audiovisual materials). Participants will be requested to read and watch the intervention package within 7 days.

The post-intervention assessment will take place 7 days after the intervention. Participants will be asked to fill in the following questionnaires: (1) the Diagnostic Delay Questionnaire; Quality of Life (2) WHOQOL-Bref and (3) EQ-5D 5L; (4) HADS; (5) BCKT; (6) Intervention Material Feedback Form.

The follow up assessment will be scheduled at 3 months (12 weeks) after the post-intervention assessment. The Participant will be requested to fill in: (1) The Diagnostic Delay Questionnaire; Quality of Life (2) WHOQOL-Bref and (3) EQ-5D 5L; (4) HADS; (5) BCKT. The researcher will review the medical record of the patient to registrate the occurence of treatment delay. This period is chosen because it is also a criterion for treatment delay.

Trained research assistants with a background of psychology will conduct the assessments. All research assistants have received a 5-days workshop covering how to administer the instruments, information on common psychosocial needs of breast cancer patients, general interview techniques, and how to take a neutral role instead of a therapeutic role. Ongoing monitoring will be conducted through regular supervision by the main researcher (HS) supervised by the principle investigators.

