**Methods:**

A cluster-randomized controlled trial will be conducted in 106 patients in four hospitals in Bandung, West Java, Indonesia. Data will be collected at baseline (pre-assessment), 7 days after the intervention (post-assessment), and at 3 months (follow-up assessments). The primary outcome is delay in diagnosis and treatment. Secondary outcomes are breast cancer knowledge, anxiety and depression, and quality of life. Exploratively, adherence with treatment will be measured too. Data will be analysed by hierarchical linear modelling (HLM) to assess differential change over time.

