## Methods

### Design

The study will be a multicentre, cluster-randomized controlled trial (cRCT), with hospitals as the unit of randomisation (clusters). We will include four hospitals in Bandung, Indonesia that have agreed to participate in this study. Because of the limited number of hospitals, we will use a cross-over design in which in each hospital will be given PERANTARA or control (treatment as usual (TAU)) at successive periods. Because every hospital forms its own control, the cross-over design can produce results with a smaller sample size than required with a parallel design. The order in which the hospital receives PERANTARA is randomly determined. The study will compare the PERANTARA to TAU in women with suspected breast cancer. This study uses two predefined periods. In the first period, two hospitals will have the experimental group (the patient is given the intervention and TAU) and two other hospitals will have the control group (patients only receive TAU). In the second period, it is the other way around.

The primary outcome is diagnosis delay in terms of the time between the date of the first consultation at the hospital and the date of final breast cancer diagnosis based on pathological examination. Secondary outcomes are breast cancer knowledge, anxiety and depression, and quality of life, as well as treatment delay.

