### Instruments

#### Primary outcome

Diagnosis delay will be the primary outcome measure. This is defined as the time between the date of the first consultation at the hospital and the date of the definite breast cancer diagnosis based on pathological examination. This outcome will be measured using the Diagnostic Delay Interviewer Guide. This instrument has been developed by the researchers and consists of the following questions: (a) What was the date that you consulted with a doctor in the hospital?, (b) What was the date that you received the breast cancer diagnosis?, and if there was a consult delay (c) What were the reasons for delay? A distinction will be made between delay due to the patient and due to the doctor. This tool will be pilot-tested before the final data collection is done.

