Quality of life will be measured using the WHOQOL-BREF ([25]; in the Indonesian version with a 4 week-time frame). This tool is a self-report questionnaire that consists of 26 items and each item represents one facet of life that is considered to have a contribution to a person’s quality of life. Two items measure quality of life and health satisfaction in general. Twenty-four items measure four broad domains, namely physical health (7 items), psychological health (6 items), social relationships (3 items) and environmental (8 items). The WHOQOL-BREF has been validated, and indicates high validity and reliability for measuring the quality of life among the elderly [26]. We will also use the EQ-5D 5L to measure health-related quality of life [27]. EQ-5D 5L is based on a descriptive system that defines health in terms of 5 dimensions: mobility (MO), self-care (SC), usual activities (UA), pain/discomfort (PD), and anxiety/depression (AD). Each dimension has 5 levels: no problems, slight problems, moderate problems, severe problems, and extreme problems/unable. This descriptive system is then followed by a self-rating of overall health status on a visual analogue scale (EQ - VAS) ranging from 0 (“the worst health you can imagine") to 100 (“the best health you can imagine"). EQ-5D 5L has been validated in diverse patient populations in numerous countries [28]. The official Bahasa Indonesia version of the EQ-5D 5L will be used; provided by the EuroQol Group [29].

Feedback from participants on the intervention material package will be measured using The Intervention Material Feedback Form. This instrument has been developed by the researchers. Finally, treatment delay will be measured at the follow-up measurement by asking the patient with a positive diagnosis if she has started her treatment at the hospital. This will also be checked with the hospital records.

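### Treatment delay has three different statuses in the protocol and, as described, is judged at a visit not tied to the diagnosis date, so a shift in diagnosis timing alone can change it

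*Protocol article*

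**What the plan says.** **Status of the outcome.** The abstract's Methods paragraph states "The primary outcome is delay in diagnosis and treatment". The Design section makes diagnosis delay the primary outcome and then says "Secondary outcomes are breast cancer knowledge, anxiety and depression, and quality of life, as well as treatment delay". The Instruments section also names diagnosis delay alone as primary and describes treatment delay under its secondary-outcome heading. The last paragraph of the Background says effects on treatment delay were explored.

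**Measurement.** The Procedure section sets two visits: "The post-intervention assessment will take place 7 days after the intervention" and "The follow up assessment will be scheduled at 3 months (12 weeks) after the post-intervention assessment". It adds "The researcher will review the medical record of the patient to registrate the occurence of treatment delay" and then "This period is chosen because it is also a criterion for treatment delay". The secondary-outcome section says treatment delay is measured at follow-up "by asking the patient with a positive diagnosis if she has started her treatment at the hospital", checked against hospital records.

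**Dates collected.** The interviewer guide for the primary outcome asks for the consultation date and "What was the date that you received the breast cancer diagnosis". It lists no treatment start date. No section says from which date the 3-month treatment-delay criterion runs.

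**The concern.** Two things are at stake.

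First, a reader cannot tell from this document whether treatment delay is primary, secondary or exploratory. The status of an outcome has to be fixed before results are known, and the abstract and the body give different answers.

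Second, a started/not-started answer at a visit anchored near enrolment does not measure time from diagnosis to treatment. A woman diagnosed early has had most of the follow-up in which to start, and a woman diagnosed shortly before the visit has had very little. The programme aims to bring diagnosis forward. If it succeeds, the arms will differ on this measure even when nothing after diagnosis has changed, and that difference could be reported as a separate effect on treatment delay.

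**Working it through.** **Status, side by side**

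| Place | Status of treatment delay |
|---|---|
| Abstract, Methods | part of the primary outcome |
| Methods, Design | secondary (diagnosis delay is primary) |
| Methods, Instruments | under the secondary-outcome heading (diagnosis delay alone is primary) |
| Background, aims | explored |

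That is three statuses for one outcome.

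**Timing of the visit.** The follow-up is 12 weeks after the post-assessment, and the post-assessment is 7 days after the intervention. This gives W = 12 + 1 = 13 weeks from enrolment, or about 14 if the 7 days allowed for reading and watching the package come first.

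**One-patient example.** Take 5 weeks from diagnosis to treatment and W = 13.
- Diagnosed in week 4: treated in week 9, so counted as started.
- Diagnosed in week 10: treated in week 15, so counted as not started, although only 3 weeks have passed since diagnosis.

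**Size in groups.** The protocol gives no figure for treatment delay and no distribution for either interval, so there is nothing to reproduce and every time below is an assumption. Let D be weeks from enrolment to diagnosis and T weeks from diagnosis to treatment. Both are exponential and independent, and T is the same in both arms. Write a = ln 2 / median D and b = ln 2 / median T.

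- P(diagnosed by W) = 1 − exp(−aW)
- P(treated by W) = 1 − [b·exp(−aW) − a·exp(−bW)] / (b − a), or 1 − exp(−aW)(1 + aW) when a = b
- Share started among the diagnosed = P(treated by W) / P(diagnosed by W)

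With W = 13 and median T = 4 weeks:
- Median D = 8: 0.457 / 0.676 = 0.676 started, so 32.4% untreated.
- Median D = 4: 0.658 / 0.895 = 0.735 started, so 26.5% untreated.
- Difference: 0.735 − 0.676 = 0.059, about 6 points, with identical T.

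For diagnosis medians of 8 vs 5, 8 vs 4, 6 vs 4 and 10 vs 6 weeks, and treatment medians of 3 to 6 weeks, the difference is 3.3 to 6.0 points at W = 13 and 3.6 to 6.2 at W = 14. An extreme contrast of 12 vs 3 weeks gives larger gaps: at W = 13 with median T = 4, untreated falls from 34.7% to 23.3%, about 11 points.

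**Measured from diagnosis instead.** P(T > 12 weeks) = 2^(−12 / median T). This is about 12.5% for a median of 4 weeks and 35.4% for 8 weeks, whatever the median time to diagnosis.

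**The direction can reverse.** Take median T = 6 weeks and W = 13, with half the women diagnosed in week 2.
- Other half diagnosed in week 15: they are not counted. Untreated share = P(T > 11) = 2^(−11/6) = 28%.
- Other half brought forward to week 12: they now count, mostly untreated. Untreated share = [2^(−11/6) + 2^(−1/6)] / 2 = (0.281 + 0.891) / 2 = 58.6%.

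Earlier diagnosis here raises the measure.

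**The case against.** **The protocol does not say the clock starts at the post-assessment.** The sentence about the period explains why the visit was placed where it is. It does not say that a woman untreated at the visit is delayed. A diagnosis date is collected and a record review is planned, so a diagnosis-to-treatment definition is compatible with the text and might sit in a fuller document. This stands in part. A reader might infer that the protocol labels women as delayed while they are still within three months of diagnosis, but no such rule is written. What is written is a started/not-started question at a fixed visit, a record check for whether delay occurred, and a rationale that equates the visit interval with the criterion. Taken as described, the measure is not anchored to diagnosis.

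**Earlier diagnosis need not lower the measure.** This stands, as the reversal above shows. A reader might infer that every gain in diagnosis time reappears as a gain in treatment delay, and that is not true in general.

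**The effect is modest and cannot arise from nothing.** This also stands. If diagnosis timing is the same in both arms, the artefact is zero, so a programme that does nothing would not look effective through this route. In the 8 vs 4 week case, suppose all 53 per arm had cancer, with no attrition or clustering. About 36 and 47 would be diagnosed by week 13, and the standard error is √(0.676×0.324/36 + 0.735×0.265/47) ≈ 0.10. The shift is then about 0.6 standard errors, and a 5% test would reject about 9% of the time. Participants are only suspected of having cancer, so fewer would contribute.

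**The status conflict is one loose abstract sentence.** The title, aims, Design and Instruments all point to diagnosis delay. A reader might infer that the trial may claim success on either of two primaries, with an inflated familywise error. The protocol states no such either-or rule and no pair of separate 5% tests, so no error-rate figure can be attached. The contradiction between abstract and Methods remains.

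**Conclusion.** The point holds in two limited parts.

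- **Status.** The contradiction is on the page and needs no assumption: primary in the abstract, secondary in Methods, explored in the aims.
- **Measurement.** As described, treatment delay depends on when diagnosis occurred as well as on how soon treatment followed. Under assumed exponential times and equal diagnosis-to-treatment time, the usual result is a fall of about 3 to 6 points in the untreated share. A rise is possible because only women diagnosed by the visit are counted.

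The consequence is that a change in diagnosis time may be misread as a change in treatment delay. It affects an outcome that the body of the protocol treats as non-primary, and it is nil if the arms do not differ in diagnosis timing. The size rests wholly on assumed intervals. That the measure depends on diagnosis timing follows from the described measurement alone.

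**What to change.** 1. Correct the abstract so that diagnosis delay is the sole primary outcome, and give treatment delay one status, secondary or exploratory, in the abstract, aims and Methods.
2. Define treatment delay as days from the date of pathological diagnosis to the date of first treatment, with the start date taken from the hospital-record review already planned.
3. Analyse it as time-to-event among diagnosed women, censoring those untreated at the date of the record check.
4. Replace the sentence justifying the 3-month visit by one that states from which date the treatment-delay criterion runs.

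**Cost.** A few wording changes and one more date to extract per diagnosed woman. The comparison stays conditional on having been diagnosed, so the arms may still differ in who is counted. It should be reported as supportive only.

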**Table 1 Tab1:**
[figure not shown]
Overview of PERANTARA Package

The prototype of PERANTARA was piloted within 13 patients and with oncologists and survivors. Results from this pilot study showed that the prototype was feasible and acceptable to use. Trained research assistants will give the PERANTARA to the experimental groups. They will give a brief explanation to the patient regarding PERANTARA and instructions on how to use it.

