#### Secondary outcome

A standard socio-demographic and medical history form (SDMH) will be used to collect patients’ background data on ethnicity, age, marital status, religion, education level, employment status, income level, travel time to hospital, insurance status, mental health status, family history of cancer and use of traditional healer. The patients’ medical records will also be reviewed to obtain data on type and stage of cancer and type of treatment.

Patient knowledge will be assessed using the Breast Cancer Knowledge Test (BCKT). The BCKT is a 20-item questionnaire that was developed and tested to determine (a) general knowledge of breast cancer; and (b) the relationship between the knowledge of breast cancer and utilization of screening practices. The BCKT consists of 2 subscales; one subscale of 12 items to measure general knowledge and one subscale consisting of 8 items to measure knowledge of curability. In the first section, item number 3 about the breast cancer prevalence was adjusted with the actual Indonesian prevalence rate. The total score ranged from 0 to 20, with higher scores indicating higher breast cancer knowledge. The BCKT has an acceptable reliability coefficient (α = 0.69). The Breast Cancer Knowledge Test (BCKT) has been translated into Indonesian using the forward-backward translation method [24].

Symptoms of anxiety and depression will be measured with the Hospital Anxiety and Depression Scale (HADS). The HADS is a 14-item self-report questionnaire that was developed to assess psychological distress in people with medical illness. It consists of 2 subscales: 7 items to measure anxiety (HADS-A) and 7 items to measure depressive symptoms (HADS-D). Psychometric properties of the Indonesian version of the HADS were adequate, with values of Cronbach’s coefficient (alpha) being 0.77 and 0.74, respectively [13].

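### One pool of research assistants both delivers PERANTARA and conducts the assessments, so the interview-based delay data may be collected by the person who delivered the intervention

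*Protocol article*

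**What the plan says.** On assessment, the Procedure section states: "Trained research assistants with a background of psychology will conduct the assessments". It adds: "All research assistants have received a 5-days workshop covering how to administer the instruments". The same workshop covered "how to take a neutral role instead of a therapeutic role", and the assistants are supervised regularly.

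On delivery, the Intervention section states: "Trained research assistants will give the PERANTARA to the experimental groups". It continues: "They will give a brief explanation to the patient regarding PERANTARA and instructions on how to use it".

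On the primary outcome, the Primary outcome section states: "This outcome will be measured using the Diagnostic Delay Interviewer Guide". The woman is asked for the date of her consultation, the date of her diagnosis and, if there was a delay, the reasons. It then says: "A distinction will be made between delay due to the patient and due to the doctor".

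On the secondary outcomes, the Procedure section has participants complete the knowledge, distress and quality-of-life scales themselves. The Secondary outcome section confirms this for distress: "The HADS is a 14-item self-report questionnaire that was developed to assess psychological distress in people with medical illness". A check against hospital records is stated for treatment delay (Procedure and Secondary outcome sections). None is stated for the dates that make up diagnosis delay.

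**The concern.** PERANTARA cannot be hidden from the women who receive it, so the main protection against biased measurement is who collects the outcomes and how. If an assistant hands over the package, explains it and later interviews the same woman about her delay, two things can go wrong. The assistant may probe dates and reasons with an expectation of benefit, and the woman may give answers that please the person who gave her the material.

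The exposed part is the primary outcome data. Dates recalled in an interview can be probed more or less hard. Deciding whether a delay came from the patient or the doctor needs judgement, and patient-related delay is what the package is meant to reduce.

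A bias of this kind follows the arm. The crossover balances stable differences between hospitals, but a bias tied to delivery moves with the intervention when the periods switch. A larger sample would not remove it either.

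**Working it through.** No arithmetic applies; the check sets the article's statements side by side.

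1. **Who delivers.** The Intervention section names trained research assistants. Delivery includes a short explanation and instructions, so it is a personal contact as well as a handover.

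2. **Who assesses.** The Procedure section names trained research assistants, without limiting them to particular assessments or arms. All of them were trained to administer the instruments. No separate assessor team and no masked assessor is described. The overlap at the level of the role is therefore stated in the text.

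3. **Whether it is the same individual.** No sentence says that the assistant who delivers to a woman also assesses her, and none says otherwise. The text supports a possibility, not a fact.

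4. **Whether the stated safeguard covers it.** Training in a neutral role concerns conduct. It neither conceals the arm nor divides the tasks.

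5. **Which outcomes are exposed.**
   - *Diagnosis delay, reasons and attribution:* collected with an interviewer guide, with no stated record check. Most exposed. The attribution is the most open to judgement; the two dates are events that can be verified.
   - *HADS, BCKT, WHOQOL-BREF, EQ-5D-5L:* completed by the participant in sessions that assistants conduct. Less exposed. Women who cannot read are enrolled (Procedure section, on consent) and would presumably need items read to them, but the article does not say how this is done.
   - *Treatment delay:* asked of the patient and checked in the records. Least exposed.

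6. **Whether separating the tasks would mask the assessor.** The Design section assigns the arm by hospital and period, so anyone working at a hospital can infer it. A different interviewer removes the personal link with the woman but does not guarantee masking.

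7. **Whether a size can be given.** The article states neither an effect size nor a standard deviation for diagnosis delay, and nothing on how far interviewers might shift the answers. No figure for the bias can be derived.

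**The case against.** The strongest reply is that a shared job title does not mean a shared person. Who covers which visit is a staffing detail that a condensed article may leave to the full protocol. A reader might infer that every intervention woman is interviewed by the person who gave her the package. The document does not support that reading. What it does state is that one pool holds both tasks and that all its members were trained to assess. The point rests on that statement, not on silence alone.

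Second, a reader might infer that only intervention women have a relation with the assistants. That is also too strong. Assistants inform all participants and obtain consent (Procedure section), conduct the assessments without distinction of arm, and track the services patients receive (Treatment as usual section). What control women lack is the delivery encounter. A wish to please the person who delivered the package is specific to PERANTARA, whereas interviewer expectation could act in both arms.

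Third, the secondary scales are already completed by participants, and the knowledge test is scored on its answers, so a courtesy answer has no obvious way to raise it. This stands, and it confines the main concern to the interview data.

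Fourth, diagnosis delay is the interval between two dated events, and the patient-versus-doctor distinction is not part of its definition. This also stands. It makes a large distortion of the primary outcome less likely, but the dates still rest on the woman's report. The Procedure section also lists a delay questionnaire among the forms that participants fill in. If that were self-completed, interviewer influence on the dates would be smaller; however, the Primary outcome section, which defines the measurement, names an interviewer guide.

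**Conclusion.** The concern holds in a limited form. The article assigns delivery and assessment to one pool of research assistants without separating the tasks. The delay dates, the reasons and the attribution to patient or doctor may therefore be collected by someone who delivered the intervention to that woman. Neutral-role training does not remove this.

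The conclusion assumes only that the role descriptions mean what they say and that the primary outcome is collected by interview, as its own section states. It does not show that any individual performs both tasks for the same woman, that the bias is confined to one arm, or that the self-completed scales are materially affected. Its size cannot be estimated from the document. It is a risk to measurement that can be reduced at modest cost, not a flaw that invalidates the trial.

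**What to change.** Three changes, using the existing assistants and records:

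1. Where staffing allows, have the post and 3-month interviews done, in person or by telephone, by an assistant who did not deliver PERANTARA to that woman. This reduces courtesy and expectation bias. It should not be described as blinding, because the arm follows hospital and period.
2. Record the reasons for delay in writing, and have the attribution to patient or doctor coded from those notes with the arm masked. Any mention of the package should be removed first.
3. Check the first-consultation and pathology-diagnosis dates against hospital records, as is already planned for treatment delay. For the primary outcome this is the most direct safeguard. The plan already includes medical-record review for type and stage of cancer.

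The cost is some travel, telephone and record-review time and less continuity between assistant and participant. All assistants are already trained in the instruments and all four hospitals are in Bandung, which helps. The article does not give the number of assistants or how they are spread across hospitals, so whether the first change needs extra staff cannot be judged from it. The second and third changes do not depend on the visit rota.
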